## Abstract

**Background:**

The incidence, mortality, and prevalence of stroke are high in China. Stroke is commonly associated with insomnia; both insomnia and stroke have been effectively treated with acupuncture for a long time. The aim of this proposed trial is to assess the therapeutic effect of acupuncture on insomnia following stroke.

**Methods:**

This proposed study is a single-center, single-blinded (patient-assessor-blinded), parallel-group randomized controlled trial. We will randomly assign 60 participants with insomnia following stroke into two groups in a 1:1 ratio. The intervention group will undergo traditional acupuncture that achieves the *De-qi* sensation, and the control group will receive sham acupuncture without needle insertion. The same acupoints (DU20, DU24, EX-HN3, EX-HN22, HT7, and SP6) will be used in both groups. Treatments will be given to all participants three times a week for the subsequent 4 weeks. The primary outcome will be the Pittsburgh Sleep Quality Index. The secondary outcomes will be: the Insomnia Severity Index; sleep efficacy, sleep awakenings, and total sleep time recorded via actigraphy; the National Institutes of Health Stroke Scale; the Stroke-Specific Quality of Life score; the Hospital Anxiety and Depression Scale. The use of estazolam will be permitted and regulated under certain conditions. Outcomes will be assessed at baseline, 2 weeks after treatment commencement, 4 weeks after treatment commencement, and at the 8-week follow-up.

**Discussion:**

This proposed study will contribute to expanding knowledge about acupuncture treatment for insomnia following stroke. This will be a high-quality randomized controlled trial with strict methodology and few design deficits. It will investigate the effectiveness of acupuncture as an alternative treatment for insomnia following stroke.

**Trial registration:**

Chinese Clinical Trial Registry identifier: ChiCTR-IIC-16008382. Registered on 28 April 2016.

## Background

The Global Burden of Disease Study (2013) found that cerebrovascular disease was the third leading cause of disability-adjusted life years worldwide [1]. Cerebrovascular disease is a major chronic disease in China, ranked third among the most common causes of death for urban residents and first for rural residents [2]. Stroke morbidity in China is 89.6–314 out of every 100,000 in men and 76.7–212.2 out of every 100,000 in women [3]. Stroke can be divided into two major types based on the type of pathological process: hemorrhagic stroke and ischemic stroke. The incidence of hemorrhagic stroke in China declined by 1.7% over a recent 21-year period, but that of ischemic stroke increased by 8.7% annually [4]. Common post-stroke complications include sleep disorders (SD), such as insomnia, sleep apnea, and daytime sleepiness [5], and SD continues to be the most unrecognized modifiable risk factor for stroke [6]. Untreated SD causes cognitive dysfunction, altered mood, sleepiness, and fatigue, and may impede stroke rehabilitation, lengthen hospital stay, influence stroke outcomes, and increase the possibility of stroke recurrence [7].

One of the most common SD associated with stroke is insomnia [5]. Insomnia is characterized by difficulty in falling asleep and staying asleep, early morning awakening, and nonrestorative sleep. The primary pharmacological treatments for insomnia are benzodiazepines, nonbenzodiazepine sedatives, and melatonin agonists. Although effective pharmacologic treatments for insomnia are available, these medications often cause side effects such as residual daytime sedation, drowsiness, dizziness, lightheadedness, cognitive impairment, motor incoordination, and dependence [8]. The mainstay of nonpharmacologic intervention for insomnia is cognitive behavioral therapy (CBT). However, CBT often causes an acute reduction in total sleep time (TST) during the first few weeks of treatment, which means that SD improvements with CBT require long-term implementation [9].

Faced with the limitations of currently available insomnia treatments, more people are seeking complementary and alternative medicine options. According to the theory of traditional Chinese medicine, acupuncture provides overall coordination to help the body achieve a state of relative equilibrium of yin and yang, restoring its physiological function and regulating the sleep-awake cycle. Recently, the frequency of visits to acupuncturists has markedly increased in the United States [10]; however, there has been little focus on research into acupuncture for insomnia following stroke. Two recent randomized controlled trials (RCTs) had shown that insomnia following stroke was positively affected by intradermal acupuncture and low-frequency electric stimulation at acupoints [11, 12]. However, these RCTs had methodological deficits, including problems with randomization, lack of sample size estimation, blinding issues, no mention of acupuncturist certification, and no use of the intention-to-treat (ITT) analysis [13]. These design deficits make their findings far from conclusive. More high-quality clinical RCTs are required to investigate the effectiveness of acupuncture treatment for insomnia following stroke. In this proposed RCT, we aim to investigate the effectiveness of acupuncture for insomnia following stroke.

## Methods/design

### Hypotheses

Participants with insomnia following stroke treated with real acupuncture will have greater improvement in sleep quality and other related symptoms than those treated with sham acupunctureThe sham acupuncture procedure can be successfully implemented in this RCT in which participants will be unaware of the group assignment

### Objectives

To compare improvement in sleep quality recorded using the Pittsburgh Sleep Quality Index (PSQI) between the intervention group and control groupTo compare changes between the intervention group and control group in the Insomnia Severity Index (ISI), actigraphy, the National Institutes of Health Stroke Scale (NIHSS), the Stroke-Specific Quality of Life (SS-QOL), and the Hospital Anxiety and Depression Scale (HADS)To evaluate the design of the sham acupuncture procedure

### Design

This is a single-center, patient-assessor-blinded, parallel-group RCT that conforms to the Consolidated Standards of Reporting Trials [14] and Standards for Reporting Interventions in Clinical Trials of Acupuncture [15] guidelines for acupuncture studies. Eligible patients will be randomly divided into the intervention group and the control group in a 1:1 allocation ratio.

The flowchart of the study process is detailed in Fig. 1. The timing of treatment visits and data collection is detailed in Table 1.

**Fig. 1 Fig1:**
[figure not shown]
Study process

**Table 1 Tab1:** Timing of treatment visits and data collection

	Baseline	Treatment phase			Follow-up phase
		Week 0	Week 2	Week 4	Week 8
Sign informed consent		×			
Medical history	×				
Randomization		×			
Intervention		×	×	×	
Primary outcome					
PSQI	×			×	×
Secondary outcomes					
ISI	×		×	×	×
Actigraphy	×		×	×	×
NIHSS		×	×	×	×
SS-QOL		×	×	×	×
HADS		×	×	×	×
Estazolam dose			×	×	×
Adverse events			×	×	×

*HADS* Hospital Anxiety and Depression Scale, *ISI* Insomnia Severity Index, *NIHSS* National Institutes of Health Stroke Scale, *PSQI* Pittsburgh Sleep Quality Index, *SS*-*QOL* Stroke-Specific Quality of Life

### Recruitment

All participants will be recruited through advertisements on micromessage (Wechat) and hospital bulletin boards in Shanghai Municipal Hospital of Traditional Chinese Medicine in Shanghai, China. If they show interest in participating, they can call the researchers with the phone number reserved. The researcher in charge of recruitment will explain the study in detail, and outline the potential benefits of this RCT to patients with insomnia following stroke. Patients who show interest in participating will be assessed according to the inclusion and exclusion criteria on their first visit. Once they agree to participate in this RCT, they will be asked to sign written informed consent before undergoing acupuncture intervention.

### Participants

Inclusion criteria: men or women aged 18–75 years who (1) meet the diagnostic criteria of ischemic stroke according to the guidelines for the diagnosis and treatment of acute ischemic stroke in China (2014) [16] in the past 2 weeks to 2 years, (2) meet the diagnostic criteria of insomnia according to the *Diagnostic and Statistical Manual of Mental Disorders*, *Fifth Edition* [17] for at least 1 month, (3) PSQI score ≥ 6, (4) ISI score ≥ 8, (5) demonstrate no problems with communication, both visual and auditory (reading, writing, hearing, speaking, and seeing), and (6) sign a written informed consent for participation in the RCT.

Exclusion criteria: (1) those who have experienced insomnia before their stroke, (2) a history of sleep apnea syndrome, (3) a history of severe neural or psychiatric disorder or major neuropsychiatric disorder (such as autism, learning disorder, or mental retardation), (4) severe primary disease of the cardiovascular, hepatic, renal, or hematopoietic system, (5) infection or inflammation at the acupoints, (6) hemorrhagic disease or anticoagulant intake, (7) those who have used Western and/or Oriental medicine in the past 2 weeks for depression, or anxiety, (8) those who have received acupuncture for insomnia in the past month, (9) those who have participated in any other clinical trial in the past 3 months, (10) those who are pregnant or breastfeeding, and women of childbearing age who are not using proper birth control, and (11) refusal to wear a wristwatch-like actigraph while sleeping.

Dropout criteria: (1) development of serious disease (such as heart disease, pneumonia, or stroke) during the observation period, (2) receiving other treatments for insomnia (such as other Western medicine, Oriental medicine, moxibustion, or massage) during the observation period, (3) participants who present with serious adverse events, (4) participants who refuse to continue to participate in the RCT, and (5) those lost to follow-up.

### Intervention

The participants from outpatient departments will receive acupuncture treatments in the outpatient clinic of the acupuncture department three times per week for 4 weeks. The inpatients will receive acupuncture treatment three times per week at the time of hospitalization, and will then receive outpatient treatment three times per week for 2 weeks. In each treatment session, every patient will be placed in a separate quiet space and asked to wear an eye-patch. Each treatment session will be 20 min. The treatment course will last for 4 weeks, and the follow-up period will be 4 weeks. All participants will receive standard Western medicine therapy for stroke, limb function rehabilitation therapy, and clinical nursing in Shanghai Municipal Hospital of Traditional Chinese Medicine. To improve adherence to intervention protocols, all participants will receive intervention and assessments by telephone reservations, and be given some financial subsidies after follow-up.

Patients in both groups will be treated with stainless steel needles (0.25 × 25 mm and 0.30 × 40 mm; Wuxi Jiajian Medical Material Co., Ltd., Wuxi, China) at the same acupoints, including *Baihui* (DU20), *Shenting* (DU24), *Yintang* (EX-HN3), bilateral *Anmian* (EX-HN22), bilateral *Shenmen* (HT7), and bilateral *Sanyinjiao* (SP6). The acupuncturist will use 0.25 × 25-mm needles for acupoints DU20, DU24, EX-HN3 and HT7, and 0.30 × 40-mm needles for acupoints EX-HN22 and SP6 (Table 2).

**Table 2 Tab2:** Details of interventions

	Intervention group	Control group
Acupoints	DU20, DU24, EX-HN3, EX-HN22, HT7, SP6	DU20, DU24, EX-HN3, EX-HN22, HT7, SP6
Depth of needle insertion	DU20, DU24, EX-HN3: 10 mm	No needle insertion
	EX-HN22, SP6: 15 mm	
	HT7: 5 mm	
Needle retention time	20 min	20 min
Needle type	Stainless steel	Blunt stainless steel
	(0.25 × 25 mm or 0.30 × 4 0 mm; Wuxi Jiajian, Wuxi, China)	(0.25 × 25 mm or 0.30 × 40 mm; Wuxi Jiajian, Wuxi, China)
Frequency and duration of treatment sessions	Three times a week for the subsequent 4 weeks	Three times a week for the subsequent 4 weeks
Needle stimulation	*De-qi* sensation	Without *De-qi* sensation

### The intervention group

The intervention group will be treated with the real tube-needling method, while lying in the supine position and wearing an eye-patch. After routine skin sterilizing, DU20, DU24, and EX-HN3 will be punctured obliquely 10 mm deep into the skin; EX-HN22 and SP6 will be punctured 15 mm deep in a direction perpendicular to the skin, and HT7 will be punctured perpendicularly to a depth of 5 mm. Licensed and experienced acupuncturists will conduct needle manipulation including lifting, thrusting, and rotating to obtain the proper needling sensation (*De-qi* sensation). Then they will stick a 2 × 2-cm piece of tape on the skin beside each needle. After a 20-min retention period, the needles and tapes will be removed simultaneously.

### The control group

The control group will receive sham acupuncture treatment. Before each session of sham acupuncture, we will prepare plastic tubes with a blunt needle inside each one. The acupuncturist will put the tube needle-end-up on the skin, and knock the tube slightly. The needles with blunt tips will not be inserted into the skin, but will create a pricking sensation similar to real acupuncture. After removing the tubes, the blunt needles will be stuck at the acupoints with 2 × 2-cm pieces of tape. After a 20-min retention period, the needles and tapes will be removed simultaneously.

Hospital Anxiety and Depression ScaleThe HADS is a validated, widely-used, 14-item self-report scale designed to briefly measure current anxiety and depressive symptoms in nonpsychiatric hospital patients [22]. It excludes somatic symptoms, therefore avoiding potential confounding factors. The HADS comprises two independent seven-item subscales for anxiety and depression
Estazolam doseThroughout this RCT, participants will be allowed to take 0.5–2 mg estazolam when they experience difficulty falling asleep for more than two consecutive days, or when they feel seriously ill because of insomnia symptoms. The dose should be recorded in the paper

### Sample size

The sample size calculation for our RCT is based on the change in the PSQI score. According to previous research [23], a sample size of 24 participants should be recruited in each group. Assuming about a 20% dropout rate, we estimate that a total of 60 participants should be recruited for this RCT.

### Randomization

We plan to use the random block method. An independent researcher, who has no contact with any participant, will use SPSS version 23.0 software (SPSS Inc., Chicago, IL, USA) to generate a random number table to divide the eligible participants in a 1:1 ratio into the intervention group and the control group. The random allocation sequence will be generated in a block of 3. The researcher will then make random allocation cards and seal each card in an opaque envelope whose number is the same as the number on the card. According to the time order in which patients are asked to go to the hospital, another researcher will arrange the patients into different groups and inform the acupuncturists of the group assignment.

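### Inpatients and outpatients with a wide range of time since stroke share one allocation list and an unadjusted t test; adjusting for both, and stratifying by setting, would gain precision at almost no cost.

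*Protocol article*

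**What the plan says.** All places are in the protocol article.

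- **Participants.** Inclusion criterion 1 takes ischemic stroke "in the past 2 weeks to 2 years". Criterion 2 requires insomnia "for at least 1 month". The first exclusion criterion removes "those who have experienced insomnia before their stroke".
- **Intervention.** There are two care settings with different paths. "The participants from outpatient departments will receive acupuncture treatments in the outpatient clinic of the acupuncture department", for 4 weeks. Inpatients start on the ward and "will then receive outpatient treatment three times per week for 2 weeks".
- **Randomization.** The independent researcher must "generate a random number table to divide the eligible participants in a 1:1 ratio into the intervention group and the control group". On block size, the section then states: "The random allocation sequence will be generated in a block of 3". Sealed numbered envelopes follow, and patients are assigned by the time order of attendance. Neither care setting nor time since stroke is mentioned.
- **Primary outcomes.** The target is the change in PSQI from baseline to week 4 and week 8. The PSQI is described as covering one month.
- **Statistical analysis.** Measurement data are compared with a t test. No covariate is named.
- **Sample size.** 24 per group, about 20% dropout, 60 in total. No effect size, SD, alpha or power is given.
- **Trial status.** Recruitment began in July 2016.

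**The concern.** All the objectives compare the arms on sleep quality or on change in the other scales. Some of these, such as NIHSS and SS-QOL, could plausibly move after stroke without acupuncture. An inpatient also changes environment during the measurement window. The two nights of actigraphy before each assessment can fall on the ward at first and at home later, and a one-month PSQI can span both.

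If setting or time since stroke predicts change, two things follow. First, the mixture adds variance to the change scores, and a plain t test leaves that variance in the error term even when the arms are perfectly balanced. Second, with 30 per arm, one arm can by chance hold clearly more patients of one kind, and an unadjusted comparison then carries that difference into the estimate. Both are avoidable, because both variables are known at entry.

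**Working it through.** **1. The plan's own figure.** 24 / (1 − 0.20) = 30 per group, 60 in total. This matches. The 24 itself cannot be rebuilt. Assuming a two-sided 5% test, it implies a standardised difference of √(2/24) × (1.960 + 0.842) = 0.81 at 80% power, or √(2/24) × (1.960 + 1.282) = 0.94 at 90%. The value 0.81 is used below.

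**2. Chance of imbalance.** The share of patients with the factor (for example, inpatients) is not stated, so 20% to 50% is assumed. Under simple 30:30 allocation of 60 patients, the number X with the factor in one arm is hypergeometric with K carriers in total. The difference in shares is |2X − K| / 30.

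| Share (K) | P(difference ≥ 20 points) | P(difference ≥ 30 points) |
|---|---|---|
| 20% (12) | 0.104 | 0.002 |
| 30% (18) | 0.158 | 0.010 |
| 40% (24) | 0.187 | 0.017 |
| 50% (30) | 0.196 | 0.019 |

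**3. Size of the shift.** Shift = imbalance × factor effect. For an assumed factor effect of 0.5 or 1.0 residual SD, a 20-point imbalance gives 0.20 × 0.5 = 0.10 SD or 0.20 × 1.0 = 0.20 SD. Against 0.81 SD, that is 0.10/0.81 = 12% or 0.20/0.81 = 25%.

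**4. Loss of precision.** A binary factor with share 0.5 and effect g raises the variance from 1 to 1 + 0.25g². The SD becomes √1.0625 = 1.03 for g = 0.5 and √1.25 = 1.12 for g = 1.0. With approximate power Φ(0.81 × √(30/2) / SD − 1.96), the results are:
- factor removed: Φ(3.14 − 1.96) = 0.88
- g = 0.5, left in: Φ(3.04 − 1.96) = 0.86
- g = 1.0, left in: Φ(2.81 − 1.96) = 0.80

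**5. Simulation.** 60 patients analysed, share 50%, 15,000 runs per scenario, true effect 0 or 0.81 SD. The t critical values make power slightly lower than in step 4.

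| Design and analysis | Type I, g = 0.5 | Type I, g = 1.0 | Power, g = 0.5 | Power, g = 1.0 |
|---|---|---|---|---|
| One list, t test (as planned) | 5.3% | 5.1% | 84.8% | 78.3% |
| One list, factor in model | 5.3% | 4.9% | 86.0% | 86.2% |
| Two lists, t test | 4.6% | 2.9% | 85.9% | 81.1% |
| Two lists, factor in model | 5.3% | 5.1% | 87.2% | 87.0% |

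In the subset of planned-design trials with an imbalance of at least 20 points, the t test's false-positive rate is 6.1% (g = 0.5) or 10.5% (g = 1.0). Power in that subset is 83.9% or 72.5%.

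**6. Limits of the check.** The simulation covers one binary factor, exact 30:30 allocation and no dropout. It does not include the further gain from adjusting for baseline PSQI. If only 24 per arm are analysed, the step 4 formula with √(24/2) gives 80% with the factor removed, against 78% and 71% with it left in, so the ordering is the same at a lower level.

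**The case against.** The strongest reply is that nothing here is wrong or contradictory. Unstratified blocked randomisation is a legitimate choice for 60 patients at one centre, and covariates are usual content for an analysis plan that is not shown. Part of this stands. If a fuller document already names these covariates, the analysis half of the point falls away. However, the article does commit to a t test, and it describes allocation operationally, down to software, block size and envelopes. Stratified allocation would need separate envelope sets, and none is described. No sentence says unstratified outright; it is the natural reading.

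The reply is also right that stratification adds little once the model is adjusted: 87% against 86% power.

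A reader might infer more than the documents support:

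- **That the design is biased or the test invalid.** It is not. Over all randomisations the type I error is about 5%. The 6–10.5% applies only to the subset of trials with a large imbalance, and chance imbalance is as likely to work against acupuncture as for it.
- **That setting and time since stroke are known strong drivers of PSQI change.** No section says so. The factor effects used here are assumptions.
- **That inpatients are the recent strokes.** No section links the two, so they must be handled as separate variables.
- **That patients enter from 2 weeks.** Insomnia must have lasted a month and must not predate the stroke, so practical entry starts at about one month.
- **That about half the sample are inpatients.** The share is not given. At 20%, the chance of a 20-point imbalance is about 10%, not 20%.

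**Conclusion.** The point holds as a matter of precision and protection against chance imbalance, not of validity. The planned unadjusted comparison gives up about 1 to 2 percentage points of power if the factor is worth 0.5 SD, and about 8 to 9 if it is worth 1.0 SD. A 20-point imbalance, expected in about 10–20% of such trials, would move the arm difference by 0.1–0.2 SD. These figures rest on an assumed factor share of 20–50% (50% for the power figures), assumed factor effects, an effect of 0.81 SD inferred from the stated 24 per group, and 60 patients analysed. If neither variable predicts change, adjustment gains nothing and costs almost nothing. Most of the benefit comes from the model, which can still be used for patients already randomised.

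**What to change.** In Statistical analysis, replace the t test for PSQI and the other continuous outcomes with a linear model (ANCOVA) containing treatment, the baseline value of the outcome, care setting at entry and time since stroke. Fix the model before unblinding, including the form in which time since stroke enters.

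In Randomization, for patients not yet randomised, prepare two sealed-envelope lists, one for inpatients and one for outpatients. Use an even block size in place of 3: a block of 3 cannot be split 1:1, so it would not balance the arms within a stratum. Keep the stratum in the model, because two lists followed by an unadjusted t test make the test conservative (type I error 2.9% for a 1.0 SD factor). With 60 patients, one stratification factor is enough; time since stroke can be left to the model.

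The cost is one or two model terms beyond baseline, one extra envelope list and possibly one incomplete block per stratum. No extra patients, visits or measurements are needed, because setting and time since stroke can be established at screening.

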### Blinding method

This is a single-blinded (patient-assessor-blinded) study. Participants will be asked to wear an eye-patch in a separate quiet space before treatment, and will remain blinded during the whole treatment. Except for the acupuncturists, all other researchers (including the statisticians, outcome assessors, and data analysts) will be blinded to the group assignment. We will attempt to validate the successful implementation of the blinding method. At first treatment, all patients will be told that the needling sensation that they are experiencing is the real sensation of acupuncture. In addition, all researchers will undergo training on the specifications of this RCT before commencement, and will strictly adhere to the separation principle of each department. The primary blinding method was successfully implemented by Lao et al. [24] in a trial to evaluate the efficacy of acupuncture treatment for postoperative oral surgery pain. We used this report as a reference to improve the design of our RCT and to ensure successful completion.

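### A block of 3 cannot deliver the stated 1:1 allocation to two arms, so the planned 30:30 split is not guaranteed

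*Protocol article*

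**What the plan says.** The Randomization section names the method ("We plan to use the random block method") and the ratio: software-generated random numbers are to "divide the eligible participants in a 1:1 ratio into the intervention group and the control group". It then fixes the block size: "The random allocation sequence will be generated in a block of 3".

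The ratio is repeated elsewhere. The Abstract (Methods) says: "We will randomly assign 60 participants with insomnia following stroke into two groups in a 1:1 ratio". The Design section says: "Eligible patients will be randomly divided into the intervention group and the control group in a 1:1 allocation ratio".

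On carrying out the allocation, the Randomization section continues: "According to the time order in which patients are asked to go to the hospital, another researcher will arrange the patients into different groups". The same researcher then tells the acupuncturists which group each patient is in. The Blinding method section, however, says that blinding covers everyone else: "Except for the acupuncturists, all other researchers", with statisticians, outcome assessors and data analysts given as included roles.

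No section mentions a third arm, an unequal ratio, stratification, varying block sizes or blocks that offset one another.

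**The concern.** A permuted block balances two arms at 1:1 only if its size is a multiple of 2. The block size and the ratio stand in the same paragraph and cannot both hold within a block. This is not a detail left to a fuller document: the article states both facts, and they conflict.

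What is at stake is mainly whether the allocation procedure can be reproduced and trusted. A reader, or the data monitoring team, cannot tell from this text what sequence was placed in the envelopes. The Background section faults previous trials in this field for problems with randomization, so the description should be right.

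A smaller conflict sits beside it. The researcher who places patients in groups and informs the acupuncturists must know the arm, yet the Blinding method section leaves only the acupuncturists unblinded.

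**Working it through.** **Inputs.** Two arms at 1:1 and N = 60 (Abstract); block size 3 (Randomization); 24 per group before about 20% dropout (Sample size).

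**The plan's own total.** 24 / (1 − 0.20) = 30 per group, and 2 × 30 = 60. The total reproduces and implies a target of 30:30.

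**Divisibility.** 1:1 needs a block size divisible by 1 + 1 = 2. Since 3 mod 2 = 1, a completed block cannot be 1:1. By contrast 60/2 = 30, 60/4 = 15 and 60/6 = 10 have no remainder, so a fixed block of 2, 4 or 6 gives exactly 30:30.

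**Arm totals with blocks of 3.** 60/3 = 20 blocks. Assume each block is 2:1 or 1:2 with probability 1/2. One arm then has 20 + K participants, with K binomial(20, 0.5).

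- P(exactly 30:30) = C(20,10)/2^20 = 184,756/1,048,576 = 0.176.
- SD of an arm total = √(20 × 0.25) = 2.24.
- P(33:27 or worse) = P(|K − 10| ≥ 3) = 0.263.
- The central 95% range of one arm is 26 to 34.

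**Cost in precision.** Relative to 30:30, the efficiency of a split (30 + x):(30 − x) is 4(30 + x)(30 − x)/60² = 1 − x²/900.

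- The mean of x² is 5, so mean efficiency = 1 − 5/900 = 0.994.
- At 33:27 it is 1 − 9/900 = 0.99; at 34:26 it is 1 − 16/900 = 0.982.
- Suppose 24:24 evaluable patients give 80% power at two-sided alpha 0.05 (assumed; the article states neither). Then 33:27 gives about 79.6%, and the average over splits is about 79.8%.

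**Predictability.** Take the six equally likely orders AAB, ABA, BAA, ABB, BAB, BBA. The third assignment is forced only when the first two are alike (AAB, BBA). That is 2/6 = 1/3 of blocks, or 1/9 = 11% of assignments. A known fixed block of 4 forces on average 4/3 assignments per block, (4/3)/4 = 33%; a known block of 6 forces 1.5/6 = 25%.

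**The case against.** The strongest reply is that little is lost. A t test does not need equal arms, allocation is still random, and with a random majority arm the average power cost is about 0.2 percentage points. That stands, and the point does not rest on power.

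It can also be said that the text is loose: it may mean three blocks of 20 (60/20 = 3), or ten 2:1 blocks offset by ten 1:2 blocks. Either would allow 30:30, but neither is written.

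Three stronger readings may tempt a reader, and the article does not support them.

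- **A 40:20 trial.** If every block favoured the same arm, the split would be 40:20, with efficiency 4 × 40 × 20/60² = 0.889. Power of 80% at 24:24 evaluable would fall to about 75% at 32:16. This requires a fixed 2:1 mix, which the repeated 1:1 statements exclude.
- **Weakened concealment from the odd size.** With a random majority arm, a block of 3 forces fewer assignments (11%) than a known block of 4 (33%) or 6 (25%). The figure for a fixed 2:1 mix is (4/3)/3 = 44%, but that mix is the one just excluded. The acupuncturists' knowledge of the arm is unavoidable and disclosed in the Discussion, and nothing says that they enrol patients.
- **Allocation before eligibility and baseline.** The wording about the order of hospital visits might suggest this. But the Randomization section speaks of eligible participants, and Table 1 puts PSQI, ISI and actigraphy in the Baseline column, ahead of randomization at Week 0. The phrase can be read as using the numbered envelopes in sequence.

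On blinding, someone must open the envelopes, and no breach of assessor blinding is shown. The conflict between the two sections is real but minor.

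**Conclusion.** The Randomization section is wrong as written: a block of 3 cannot be 1:1 across two arms, and the article gives no rule that would restore 30:30 over the 20 blocks. If the majority arm is random per block, exact balance has probability 0.18 and a split of 33:27 or worse has probability 0.26. These figures rest on that assumption, since the article does not say how a block of 3 is composed. Precision is hardly affected (mean efficiency 0.994), and the total of 60 is unaffected. The fault lies in a stated method that does not deliver the stated ratio, with a secondary inconsistency over who is unblinded. Whether the sequence in use is itself unbalanced, or the block size is only misprinted, cannot be settled from the article.

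**What to change.** 1. Have the independent researcher who generated the sequence check it, and report the block size and composition actually used. The Trial status section says that recruitment began in July 2016, so this comes before any envelope is replaced.
2. If the sequence was balanced and the text is a misprint, correct the stated block size and leave the envelopes alone.
3. If blocks of 3 were really used, generate only the unused envelopes with even block sizes. Any even size resolves the contradiction; sizes of 4 and 6 in random order, withheld from recruiting, treating and assessing staff, would also limit prediction. Report the scheme used before the change.
4. Reconcile the Randomization and Blinding method sections: state that the researcher who assigns groups and informs the acupuncturists is unblinded and takes no part in recruitment or outcome assessment.

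The cost is a short amendment and, only in the third case, a new set of unused envelopes. No extra patients or procedures are needed.
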